##### Control group

An educational group therapy focusing on damage caused by alcohol, strategies to control alcohol consumption and to reduce alcohol consumption risks. This will be offeredin 4 sessions (2 h, twice a month), without focusing on manipulation of consumers or marketing strategies.

##### Intervention group

An educational group therapy focusing on damage caused by alcohol, strategies to control alcohol consumption and to reduce alcohol consumption risks. They will be offered in 4 sessions (2 h, twice a month), with the inclusion of a specific session focusing on manipulation of the consumer, marketing strategies and counter-marketing. The session content will be developed according to the results of the qualitative analysis. It will present explanations concerning alcohol marketing strategies and documents regarding alcohol marketing influences. Then participants will be asked to develop cognitive alternatives to identify and fight against the influence of alcohol marketing strategies.

The impact will be analysed to examine thepatients’ perception of their ability to control their alcohol consumption and to control alcohol craving at the end of the group sessions and 3 months later.

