**Methods:**

Our main objective isto evaluate the impact of marketing on a population with an AUD. The methodology was in 4 steps: step 1 is a pre-test (*N* = 100) selecting type of alcohol consumed and type of marketing stimuli identified by patients aged 18 + with an AUD. Step 2 is a qualitative study (*N* = 20), with in-depth interview, to understand links between alcohol marketing and patients with AUD behaviours. Step 3 is a quantitative study(*N* = 600) to confirm these links and the impact of alcohol marketing on patients with AUD behaviours. Step 4 is an interventional step, including and testing the impact of demarketing intervention on patients with AUD while using the results of the three first steps (*N* = 120).

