#### STEP 4: intervention study

The main objective of this randomized, controlled interventional stepwill be to compare the impact of an intervention which includes counter-marketing (focusing on alcohol marketing strategies and manipulation of the consumer) on the ability of drinkers with AUD who seektreatment to take control of their alcohol craving.

This intervention is a therapeutic innovation, based on inoculation theory [39]. It is possible to effectively protect citizens from harmful alcohol consumption by presenting them with this type of marketing and pointing out the ways in which it influences them. The theoretical foundations of “counter-marketing” are derived from inoculation theory, which postulates that the reinforcement of certain beliefs and attitudes - the feeling of being manipulated by marketing - will allow resistance to advertising cues [40]. The principle is based on the biological analogy of vaccination, as in the case of the “Truth” anti-tobacco prevention campaign in the United States, which has been shown to be effective in reducing adolescent smoking [41]. Inoculation messages operate in such a way that people can be protected from future attempts at persuasion by messages that warn them of the impending threat to their standpoint and refute anticipated, opposing arguments [42, 43]. Key mechanisms involved in the inoculation include an increase in the perception of threat and a greater capacity for counter-arguing against persuasive arguments [44]. Meta analyses have shown that narratives have persuasive effects on changesin attitude, intentions and behaviour [45, 46]. They may lead to persuasion by generating emotional connections with a story involving characters or with offering a high level of engagement [47]. Group interactions whichinclude drinkers with AUD who are seeking treatment, will help to deliver narratives with emotional engagement that can facilitate persuasion and inoculation.

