The intervention will be offered during the inclusion period of 1 year to every drinker with an AUD who seeks treatment in follow-up,as an out-patient, at Brest UniversityHospitaland who fulfils the inclusion criteria and is consulting at Brest UniversityHospital. Intervention will be presented as a series of therapeutic educational group meetings; the objective is to involve drinkers, to help them to make their decisions, and to help them to reduce alcohol consumption risks. Therapeutic educational groups respond perfectly to these criteria [48].

Four sessions will be organised to facilitate participation and limit the number lost to follow-up. Group meetings will be organised every 2 weeks; they will last 2 h; a nurse specialising in addictive disorders and a physician will lead the groups.

After their consent, a randomisationprocedure will select 2 groups to be compared. Participants will be randomized 1:1: control group / intervention group. The Data Management Unit (UGD) of the Brest CHRU will be responsible for the randomization (computer-generated random numbers).

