### Statistical analysis

#### Observational study (step 3)

We will first perform a descriptive analysis of the sample. Quantitative variables will be summarised by mean and standard deviation if they are normally distributed; otherwise, by median first and third quartiles. Qualitative data will be summarised by counts and proportions. Comparative multivariate analyses will be performed to determine variables associated with several patient profiles. With a 5% alpha risk and 95% power, to be able to detect small effect sizes in a multivariate analysis (F-squared of 0.05) using 20 parameters a sample size of 600 patients will be necessary.

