#### Intervention study (step 4)

As a secondary objective, inter-group comparative analyses will be performed before and at the end of the intervention on the principal outcome on a small subsample.

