On atherapeutic level, this study will be innovative, with the development of counter-marketing messagesamong drinkers on an AUD program. This study will help to build the content of the educational intervention, including alcohol counter-marketing strategies. In addition, it will make it possible to identify whether this type of focusis useful in treating patients’craving and their perception of their ability to stop consuming alcohol. If this study shows that this kind of intervention improves outcomes for drinkers with an AUD, it will be necessary to develop strategies of this type for drinkers receiving AUD care. Alcohol use disorders are complex diseases:vulnerability factors are a combination of individual factors (gender, psychiatric disorders, familial history of addictive disorders..); environmental factors (social integration, social entertainment, professional and familial status..) and factors linked to alcohol (type of alcohol, social status, damage ..) Alcohol marketing interferes with the environmental factors, because it induces unconscious, daily exposure on multiple occasions, to alcohol marketing cues. It also interferes in factors linked to alcohol, because it maintains the status of alcohol, and positive social attitudes towards it, and it plays down the risks considerably. So in order to reduce the impact of marketing high-risk products,to these vulnerable patients, it would be invaluable to be able to show individuals how they are being affected by marketing without their knowledge, and to provide them with tools to resist such marketing. The hypothesis is that this intervention on demarketing, combined with a therapeutic educational program which targets strategies to control alcohol consumption, will help to give patients a better perception of control. It would help patients with an AUD to better resist alcohol advertising stimuli [40]. Such work has never been carried out in the field of alcohol use, nor on populations with problematic alcohol consumption.

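### Step 4: the design text and the analysis section disagree on the outcomes and post-treatment times to be compared, and no outcome is designated as principal

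*Protocol article*

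**What the plan says.** Three places in the protocol article describe what Step 4 will compare.

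- *STEP 4: intervention study* gives the main objective. The two programmes are compared on drinkers' ability "to take control of their alcohol craving". No time is attached.
- *Intervention group* says that impact will be analysed on perceived "ability to control their alcohol consumption and to control alcohol craving at the end of the group sessions and 3 months later".
- *Intervention study (step 4)*, under *Statistical analysis*, is one sentence. It places the comparison among the secondary aims and says that "inter-group comparative analyses will be performed before and at the end of the intervention on the principal outcome on a small subsample".

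The *Discussion* describes the expected benefit in terms of craving and patients' "their perception of their ability to stop consuming alcohol". No section labels an outcome as principal or attaches a time to one.

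**The concern.** The analysis section refers to a single principal outcome, but the design text lists two outcomes without ranking them. The analysis section also lists the times at which arms are compared, and it leaves out the three-month time that the design text promises.

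Two things are at stake.

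- **Use of the three-month data.** An analyst who followed the statistical section literally would make the randomised comparison without the three-month assessment. Step 4 rests on inoculation against later persuasion, and the article's fourth secondary objective mentions preventing relapse. An assessment some time after the sessions is the more informative one for whether an effect persists.
- **Which result decides.** If the principal outcome and its time are not fixed in advance, the label can be given to whichever contrast looks best once data are in.

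**Working it through.** **What each place fixes**

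| Place in the article | Outcome | Post-treatment time |
|---|---|---|
| *STEP 4: intervention study* (main objective) | control of craving | not stated |
| *Intervention group* | perceived control of consumption; control of craving | after the sessions; three months on |
| *Intervention study (step 4)* (analysis) | one principal outcome, not named | end of intervention only |

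The analysis section also mentions a comparison before the intervention. That is a baseline comparison, so the end of the intervention is its only post-treatment time.

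**How many candidate tests**

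- Design text governs: 2 outcomes × 2 times = 4 contrasts.
- Analysis section governs the time, outcome left open between the two: 2 contrasts.
- Analysis section governs the time, main objective taken to name the outcome: 1 contrast.

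**Illustrative false-positive risk**

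The article gives an alpha for Step 3 only ("With a 5% alpha risk and 95% power, to be able to detect small effect sizes in a multivariate analysis (F-squared of 0.05"), so a two-sided 5% is an assumption here. For k independent tests, any of which could be called decisive without adjustment, the risk is 1 − 0.95^k:

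- k = 1: 5%
- k = 2: 1 − 0.95² = 1 − 0.9025 = 9.75%
- k = 4: 1 − 0.95⁴ = 1 − 0.8145 = 18.5%

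Related perceptions in the same patients will be positively correlated. A simulation of equally correlated normal test statistics (one million draws, critical value 1.96) gave:

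| Assumed correlation | Any of 2 | Any of 4 |
|---|---|---|
| 0.3 | 9.5% | 17.4% |
| 0.5 | 9.1% | 15.6% |
| 0.7 | 8.4% | 13.1% |

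**Cost of adjusting instead of naming one test**

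The abstract gives Step 4 a sample of 120, and "Participants will be randomized 1:1: control group / intervention group", so 120 / 2 = 60 per arm. No effect size, SD, power or dropout is stated for Step 4, so 120 cannot be reproduced and the following is illustration. With no dropout, no allowance for clustering by therapy group, and 80% power, the detectable standardised difference is (z for alpha + z for power) × √(2/60):

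- One test at 0.05: (1.960 + 0.842) × 0.1826 = 0.51. Power for an assumed difference of 0.5 SD is 78%.
- Bonferroni over four, 0.05 / 4 = 0.0125: (2.498 + 0.842) × 0.1826 = 0.61. Power for 0.5 SD is 60%.

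Fixing one principal test in advance avoids both the inflation and this loss of power.

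**The case against.** The strongest reply is that this is a condensed article. Instruments, formal endpoint labels, secondary times and handling of multiplicity commonly sit in a full protocol or SAP, and the study design figure is not available to check. The analysis sentence can also be read as covering the principal comparison alone, with the three-month assessment as a further analysis. Step 4 has one main objective, control of craving, which is the natural meaning of the principal outcome. Finally, the analysis section itself calls the comparison secondary and on a small subsample.

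Much of this stands, and it rules out several stronger readings that a reader might infer:

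- **That the three-month data will go unused, or that the question of a lasting effect is lost.** The design text still promises an analysis at three months. The analysis section omits it but does not withdraw it.
- **That the principal outcome could be anything.** The main objective points to control of craving. What is absent is the designation and its time. The *Discussion* wording about stopping drinking describes expected usefulness and is weak evidence of a rival endpoint.
- **That only the three-month assessment can serve the aim.** Resistance skills can be assessed when the sessions finish, and relapse is not listed as an outcome in either Step 4 text.
- **That the trial's error rate is 18.5%.** That figure needs independence, an alpha not stated for Step 4, and freedom to call any of four tests decisive. It also cannot be held together with a claim that the three-month data are not compared.

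The reply does not remove the mismatch. Two sections of the same article state what Step 4 will compare, and they differ on the number of outcomes and on the post-treatment times. Condensation may explain missing detail, but not two differing statements.

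**Conclusion.** The point holds as an internal inconsistency. The main objective, the design text and the analysis section for Step 4 do not agree, no outcome is designated as principal, and the three-month assessment has no stated role in the analysis section.

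The possible size is a false-positive risk of about 13% to 17% instead of 5%, if one of four unadjusted contrasts were picked afterwards and their correlation lay between 0.7 and 0.3. If only the outcome were open, the risk would be about 8% to 10%. If the main objective is taken as the designation and the analysis section as the time, there is no inflation. These figures rest on an assumed two-sided 5% and assumed correlations; they show what is at risk and do not estimate what will happen. No figure stated in the article is shown to be wrong by this point.

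This should be fixed. It is not critical, because the likely principal outcome can be inferred and the three-month analysis is still promised.

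**What to change.** Reconcile the three Step 4 texts as follows.

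1. Designate control of craving, from the main objective, at the end of the intervention, from the analysis section, as the principal outcome and time.
2. Name perceived control of consumption, and the three-month comparison, as secondary.
3. State that the arm difference will be estimated at both post-treatment times with adjustment for the baseline value. One repeated-measures mixed model with arm, time, arm-by-time interaction and baseline value would do this; other baseline-adjusted analyses are also acceptable.
4. Use the same outcome names and times in *STEP 4: intervention study*, *Intervention group* and *Intervention study (step 4)*.

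The cost is wording only. Both assessments are already planned, and no visit or patient is added. Control of consumption gives up any claim to be the principal outcome, and the three-month result is reported as secondary evidence on persistence. The changes should be made before any Step 4 outcome data are seen.

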### Study design

Study design is presented in Fig. 1.

### Statistical analysis

#### Observational study (step 3)

We will first perform a descriptive analysis of the sample. Quantitative variables will be summarised by mean and standard deviation if they are normally distributed; otherwise, by median first and third quartiles. Qualitative data will be summarised by counts and proportions. Comparative multivariate analyses will be performed to determine variables associated with several patient profiles. With a 5% alpha risk and 95% power, to be able to detect small effect sizes in a multivariate analysis (F-squared of 0.05) using 20 parameters a sample size of 600 patients will be necessary.

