Drawing on thesefindings, this study was designed in collaboration with researchers specialising in addictive disorders, in social marketing and in primary care. It is funded by the French National Cancer Institute (INCA). This study will evaluate the impact of alcohol marketing on drinkers with an AUD who are seeking treatment, using a mixed methodology in four steps. The hypotheses are that 1/ patients with an AUD are sensitive to alcohol marketing strategies because of their AUD and in proportion to the severity of their disorder, 2/ the impact of marketing tools differs according to the type of technique used (ads in public places, product placement in films and series, prices, promotions, etc.), 3/ the marketing of alcohol products influences different factors that contribute to the consumption of drinkers with an AUD who are seeking treatment (affective reactions, social norms, etc.), 4/ exposure to marketing of alcohol brands may be a triggering factor, sustaining or aggravating a higher craving among this particular category of consumers, and that, 5/ the development of interventions that focus on the manipulation of consumers and the effect of the marketing of alcohol products (i.e. demarketing strategies). This could have relevance for drinkers with AUD who are seeking treatment in order to increase their resistance skills and prevent them from relapse.

This article presents the protocol; it follows the Standard Protocol items: recommendations for Interventional Trials (SPIRIT) 2013 guidelines [34].

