## Methods/design

### Aim of the study

The primary objective is to evaluate the impact of alcohol marketing on drinkers with an AUD who are seeking treatment.

The secondary objectives are 1/ to determinethe impact of marketing according to type of marketing tools, 2/ to identify how the marketing of alcohol products influences consumption in drinkers with an AUD who are seeking treatment, 3/ to evaluate the links between exposure to marketing and alcohol craving, 4/ to develop interventions that focus on the manipulation of consumers and the effect of the marketing of alcohol products (i.e. demarketing strategies) for drinkers with AUD who are seeking treatment in order to increase their resistance skills and prevent relapse.

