#### STEP 3:quantitative observational study

Through the in-depth thematic analysis of the interviews, a questionnaire will be constructed, in collaboration among researchers specialising in addictive disorders, researchers specialising in social marketing and primary care and methodologists.

The questionnaire will collect data regarding 1/ Sociodemographic elements 2/ AUD severity and damage, history of AUD and history of treatment 3/ respondents’ responses to pre-selected alcohol marketing tools and advertising cues during Step 2. The responsesevoked when confronted with these stimuliwill be collected. They should encompass: perceptions, emotions, craving, desire to consume, perceptions of risks related to alcohol. At the end of the questionnaire, all participants will be given an explanatory document presenting data on the manipulation of consumers and the effect of the marketing of alcohol products on alcohol consumption. The questionnaire will be tested in a pilot study to ensure it is comprehensive and understandable.

This questionnaire will be offered by physicians specialising in addictive disordersto drinkers with an AUD who are seeking treatment in three university centres for addictology in France: CHU BREST, CHU NANTES, HOSPITAL PAUL BROUSSE-VILLEJUIF. During an inclusion period of 6 months, drinkers seeking treatment, who fulfilthe inclusion criteria and who have given their written consent, will complete the questionnaire in the addictive disorders centres participating in the study. Six hundred patients will be included in this step.

All the questionnaireswill be analysed (descriptive and univariate and multivariate comparative analysis) by a researcher specialising in statistics.

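### The multivariate analysis stated for Step 3 targets undefined patient profiles and gives no contrast between marketing tools, and the N = 600 statement names no outcome and falls slightly short of 95% power as printed

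*Protocol article*

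**What the plan says.** In the protocol article, the section on the statistical analysis of the observational study (step 3) plans a description of the sample and then one multivariate aim: "Comparative multivariate analyses will be performed to determine variables associated with several patient profiles". It does not say what a profile is, how many there are, or which variable is the outcome. The next sentence sizes the step: "With a 5% alpha risk and 95% power", in order to "detect small effect sizes in a multivariate analysis (F-squared of 0.05) using 20 parameters a sample size of 600 patients will be necessary".

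The section describing Step 3 itself adds only that all questionnaires receive a "descriptive and univariate and multivariate comparative analysis) by a researcher specialising in statistics". The same section lists what is recorded when patients meet the pre-selected tools and cues: perceptions, emotions, craving, desire to consume and perceived risk. AUD severity is also collected.

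The first secondary objective, under Aim of the study, is to determine the "impact of marketing according to type of marketing tools". Hypothesis 2, in the Background, is that "the impact of marketing tools differs according to the type of technique used". The abstract gives Step 3 the task of confirming the links found in Step 2 and the impact of marketing.

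**The concern.** The stated analysis and the stated question are at different levels. Asking which variables go with a patient profile is a question about differences between patients. Asking whether posters, films, prices or promotions differ in impact is a question about differences between tools, answered within patients because each respondent meets several cues. Tool type is not a characteristic of a patient, so it cannot be an explanatory variable for a patient's profile.

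The power sentence follows directly on the profile sentence but is attached to no named outcome. A reader cannot tell what the 95% power is for.

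At stake is the confirmatory yield of the largest step. The Discussion wants results that support limits on media, content, pricing and brand strategies. That argument needs estimates by tool with their uncertainty, and the stated multivariate analysis does not plan any.

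**Working it through.** **1. Question, data and analysis side by side.**

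| Element | Unit of comparison | Place in the protocol article |
|---|---|---|
| Objective 1 and hypothesis 2: impact by type of tool | Tool, within patient | Aim of the study; Background |
| Data: responses to several tools and cues | Several cues per patient | STEP 3 |
| Multivariate aim: variables associated with profiles | Patient | Statistical analysis, step 3 |

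The data would support a tool contrast, but the stated multivariate aim does not contain one. Responses to individual tools could be among the 20 parameters. Even so, their coefficients would describe how each response relates to a profile, not how the mean response differs from tool to tool.

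**2. Reproducing N = 600.** Inputs from the statistical analysis section: alpha 0.05, power 0.95, f-squared 0.05, 20 parameters, N = 600. Assumption: an omnibus F test of all 20 predictors in a multiple linear regression, since the article does not name the test.

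- Numerator df u = 20; denominator df v = N − 21; noncentrality λ = f² × N.
- Power = P[F′(u, v, λ) > F(0.95; u, v)], where F′ is the noncentral F distribution.

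As printed, f² = 0.05:
- N = 600: v = 579, λ = 0.05 × 600 = 30.0, critical F = 1.589, power = 93.7%.
- Smallest N for 95% power: 631 (v = 610, λ = 31.55, power 95.03%). N = 630 gives 94.99%.
- 631/600 = 1.052, so the shortfall is 31 patients, or about 5%.

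Reading 0.05 as R-squared:
- f² = R²/(1 − R²) = 0.05/0.95 = 0.0526.
- N = 600: λ = 0.0526 × 600 = 31.58, power = 95.02%. N = 599 gives 94.98%, so 600 is exactly the smallest sufficient N.

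Other readings at f² = 0.05 do not give 600: 19 predictors need 619, 18 predictors need 607, and using λ = f² × v with 20 predictors needs 651.

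The likeliest origin of 600 is therefore a linear-regression test at R-squared 0.05, printed as f-squared 0.05. This is an inference from the exact match; the article does not say so.

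**3. Does that calculation fit the profile analysis?** This depends on a definition that the article does not give.
- Profiles as a continuous score: the regression calculation fits.
- Two profiles compared on 20 variables by a discriminant (Hotelling) test: the F test is algebraically the same, with power 93.7% at N = 600.
- Three or more groups compared by MANOVA, with f-squared on the Pillai scale: power is above 99%.
- Nominal outcome with K profiles, likelihood-ratio test on 20(K − 1) df, assuming the total noncentrality stays at 30: power is about 94%, 84%, 75% and 67% for K = 2, 3, 4 and 5.

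The range runs from about 67% to above 99%, so no single figure can be set against the stated 95%.

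**The case against.** The strongest reply is that this is a condensed article. Model form, outcome scale and covariates commonly sit in the analysis plan, and the Step 3 questionnaire is still to be built from Step 2. That stands as far as detail is concerned: the absence of a full model specification is no finding. What remains is that the article does state a multivariate target and a power basis, and neither is connected to the tool comparison in its own objectives.

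A second reply is that the Step 3 section also provides for descriptive and univariate analysis, and that Steps 1 and 2 explore which tools patients notice and react to. This stands too. A reader might infer that the study yields no information on tools at all; the documents do not support that. What is absent from the stated plan is a model-based estimate of the difference. Likewise, AUD severity is collected and may be one of the 20 parameters, so it cannot be said that the severity gradient goes unexamined.

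A reader might also infer that f-squared cannot apply to profiles and that true power is far below 95%. The documents do not support this either, because they never say that profiles are categories or cuts of a response score. Any large loss of power obtained by cutting a continuous score follows from that assumption.

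**Conclusion.** The concern holds in a limited form. The only multivariate aim stated for Step 3 does not address the difference between marketing tools that objective 1 and hypothesis 2 ask about, although the data for it are to be collected. This rests on the text alone and needs no numerical assumption beyond each patient responding to more than one tool.

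The power statement has two smaller defects. It names no outcome. As printed it is also slightly off: 93.7% power at 600 instead of 95%, or 631 patients instead of 600, assuming an omnibus linear-regression test of 20 predictors. The gap of 1.3 percentage points is no threat to the study by itself. It disappears if the effect size was meant as R-squared 0.05.

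Whether the calculation suits the profile analysis is undetermined. It should be settled by defining the profiles, not by calling the calculation invalid.

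**What to change.** 1. Add as the main Step 3 analysis a linear mixed model of the per-cue response score (for example craving). Fixed effects: tool type as within-patient factor, AUD severity, tool × severity interaction, and centre. Random effect: a patient intercept. The tool terms address objective 1 and hypothesis 2; severity and its interaction address hypothesis 1.
2. Keep the profile analysis as secondary, and define the profiles.
3. Name the outcome to which the power statement refers and restate the figure: either R-squared 0.05 (f-squared 0.0526) with 95% power at 600, or f-squared 0.05 with 93.7% power at 600.
4. Optionally, rotate the order of cues across questionnaire versions, so that tool type is not mixed up with position or with craving carried over from the previous cue. The article fixes no cue order, so this is a low-cost safeguard and not the correction of an error.

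Cost: analysis wording and, if item 4 is taken up, a few questionnaire versions. These changes call for no extra patients. The downsides are a slightly more complex model and, if f-squared 0.05 is kept, a slightly less favourable stated power. Power for the tool contrast itself cannot be computed from the article, which gives neither the number of cues per patient nor the within-patient correlation; it should be worked out once the questionnaire is built.
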